## **7.2.2 Mechanical ventilation and recruitment maneuvers**

### *Mechanical ventilation*

Mechanical ventilation will be administered through the anesthesia ventilators in use in each individual center participating in the study. Patients will undergo volume-controlled mechanical ventilation with the lowest possible oxygen fraction (but at least 0.4) to maintain an oxygen saturation of 93% or higher, an inspiratory to expiratory ratio (I:E) of 1:2 and a respiratory rate adjusted to normocapnia (end-tidal carbon dioxide partial pressure between 35 and 45 mmHg). It is left to the discretion of the attending anesthesiologist to use a higher fraction of inspired oxygen.

Tidal volume will be set to 7 ml/kg Ideal Body Weight (IBW). The IBW is calculated according to a predefined formula: 50 + 0.91 x (centimeters of height – 152.4) for males and 45.5 + 0.91 x (centimeters of height – 152.4) for females. Tidal volume throughout this protocol refers to the actual inspired tidal volume in the ventilator circuit.

The PEEP level is selected according to the randomization group, i.e. 4 cmH2O with the lower PEEP level, and 12 cmH2O with the higher PEEP level.

### *Recruitment maneuver*

The recruitment maneuver, as part of the protective strategy, will be performed directly after induction of anesthesia, after any disconnection from the mechanical ventilator, every one hour during surgery, and before end of surgery, in a hemodynamically stable situation as

judged by the anesthesiologist. The recruitment maneuver is not easily applied with available anesthesia ventilators since not all machines have an inspiratory hold function and adequate facilities. To obtain standardization among centers, recruitment maneuvers will be performed in volume-controlled ventilation, as follows:

1. Set peak inspiratory pressure limit to 55 cmH2O
2. Set tidal volume to 7 ml/kg IBW and respiratory rate to 6 or higher breaths/min, while PEEP is 12 cmH2O (or higher if during rescue)
3. Set inspiratory to expiratory ratio (I:E) to 1:1
4. Increase tidal volume in steps of 4 ml/kg IBW until plateau pressure reaches 40 – 50 cmH2O
5. If the maximum tidal volume allowed by the anesthesia ventilator is achieved and the plateau pressure is lower than 40 cmH2O, increase the PEEP as needed, but maximum 20 cmH2O
6. Allow three breaths while maintaining plateau pressure of 40 – 50 cmH2O
7. Set respiratory rate, I:E, inspiratory pause and tidal volume back to pre-recruitment values, while maintaining PEEP at 12 cmH2O (or higher if during rescue)
- 8.

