### *Randomization arms*

Central randomization with the use of a permuted-block randomization list (block length 6) will be used. Before surgery patients will be randomly assigned 1:1 to mechanical ventilation with PEEP of 4 cmH2O without recruitment maneuvers (the “lower PEEP level”) or mechanical ventilation with PEEP of 12 cmH2O with the use of recruitment maneuvers (the “higher PEEP level”). If desaturation, defined as SpO2 ≤ 92% for > 1 min, occurs, rescue is performed according to the sub-section “Rescue Therapy”. Both strategies were chosen taking into account a recent national survey in France, most recent randomized clinical trials on mechanical ventilation of obese patients undergoing surgery and expert consensus, which was obtained during a meeting of the Respiration Subcommittee at Euroanaesthesia 2013 in Barcelona, Spain.

At each site at least two investigators will be involved: one who will be aware of the allocated intervention and collect intra-operative data; the other who will remain blinded to the intra-operative interventions and evaluate the outcomes, scoring postoperative pulmonary and extrapulmonary complications.

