#### *Protocol deviation*

Anesthesiologists may deviate from the ventilation protocol at any time if concerns about the patient's safety arise, or upon the surgeon's request.

If one of the following complications occurs and is unresponsive to specific conventional therapy, PEEP may be modified according to the anesthesiologist's judgment:

- Systolic arterial pressure lower than 90 mmHg for more than three minutes and unresponsive to fluids and/or vasoactive drugs
- New arrhythmias unresponsive to the treatment suggested by the Advanced Cardiac Life Support Guidelines
- Need for a dosage of vasoactive drugs at the tolerance limit, as judged by the anesthesiologist
- Need of massive transfusion, defined as replacement of >100% blood volume in 24 hours or >50% of blood volume in 4 hours (adult blood volume is approximately 70 mL/kg), to maintain Hct > 21% (Hb > 7 mg/dl)
- Life-threatening surgical complication

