| 7                                                                                                                                                                                                | 0.8              | 18 cmH 2 O       |
| 8                                                                                                                                                                                                | 0.9              | 18 cmH 2 O       |
| 9                                                                                                                                                                                                | 1.0              | 18 cmH 2 O       |
| 10                                                                                                                                                                                               | 1.0              | 20 cmH 2 O (+RM) |
| (+RM), recruitment maneuver optional
*At any step: If $SpO_2$ deteriorates further in an otherwise hemodynamic stable patient, consider reducing the PEEP to 10 and then 8 cmH 2 O |                  |                             |

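### The only recruitment-maneuver procedure is written for PEEP of 12 cmH2O or higher and contradicts two rescue rules that put patients below that level

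*Protocol*

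**What the plan says.** All of the text is in protocol section 7.2.2, apart from the definition of the arms in section 7.2.1.

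- **Arms (7.2.1, Randomization arms).** The lower arm is "mechanical ventilation with PEEP of 4 cmH 2 O without recruitment maneuvers". The higher arm is PEEP 12 cmH2O with maneuvers.
- **Procedure (Recruitment maneuver).** One procedure is given: "To obtain standardization among centers, recruitment maneuvers will be performed in volume-controlled ventilation, as follows". Step 2 applies "while PEEP is 12 cmH 2 O (or higher if during rescue"). Step 7 returns respiratory rate, I:E ratio, inspiratory pause and tidal volume to their earlier values, "while maintaining PEEP at 12 cmH 2 O (or higher if during rescue").
- **Schedule (Recruitment maneuver).** "The recruitment maneuver, as part of the protective strategy, will be performed directly after induction of anesthesia", then after any disconnection from the ventilator, and "every one hour during surgery, and before end of surgery, in a hemodynamically stable situation as" judged by the anesthesiologist.
- **Lower-arm rescue table.** Steps 1 to 8 carry no maneuver. Step 9, the last, has PEEP 7 cmH2O with a maneuver marked as optional.
- **Higher-arm rescue table.** PEEP runs from 14 to 20 cmH2O. A footnote covers any step: if saturation falls further in a patient who is otherwise hemodynamically stable, "consider reducing the PEEP to 10 and then 8 cmH 2 O".
- **Protocol deviation.** Departure from the ventilation protocol is allowed at any time for safety or at the surgeon's request. After listed complications that do not respond to treatment, "PEEP may be modified according to the anesthesiologist's judgment".

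**The concern.** PEEP level together with recruitment maneuvers is the randomized intervention, so the text that delivers it should give one answer for every patient state that the protocol creates. The procedure has no branch for a patient whose PEEP is below 12, although two rescue rules produce such patients.

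Two things are at stake. The first is the separation of the arms. A lower-arm patient given the optional maneuver exactly as written would leave it on the PEEP that defines the other arm. The second is consistency. Section 6.1 expects about 90 centers. Some may follow the procedure literally, others may return to the PEEP in use before the maneuver, and others may stop doing maneuvers once PEEP has been lowered. The delivered contrast, and what is recorded as a deviation, could then differ by site for reasons unrelated to the patient.

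**Working it through.** The point rests on comparing stated PEEP values. It does not depend on the sample size, power or alpha figures.

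**Step 1: what PEEP the procedure leaves.** Step 2 and step 7 both name 12 cmH2O, or more during rescue. Step 7 lists four settings that revert, and PEEP is not one of them. Step 5 allows PEEP to be raised within the maneuver, up to 20, so step 7 is the only line that settles the PEEP afterwards.

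**Step 2: which patients fit.** A higher-arm patient at 12 fits. So does a higher-arm rescue patient at 14 to 20, which is the range that the words about rescue match. Patients below 12 do not fit, and the rescue wording does not help them, because it only permits values above 12.

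**Step 3: the rules side by side (PEEP in cmH2O).**

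| Situation | PEEP before maneuver | PEEP after, as written | Change |
|---|---|---|---|
| Lower arm, rescue step 9, optional maneuver chosen | 7 | 12 | 12 − 7 = +5 |
| Higher arm, footnote, first reduction | 10 | 12 | 12 − 10 = +2 |
| Higher arm, footnote, second reduction | 8 | 12 | 12 − 8 = +4 |

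**Step 4: effect on the contrast.** The assigned contrast is 12 − 4 = 8 cmH2O. At lower-arm step 9, against the assigned higher-arm level, it is 12 − 7 = 5. After a maneuver done there as written, it is 12 − 12 = 0.

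**Step 5: is a footnote patient exempt from the schedule?** Maneuvers require hemodynamic stability. The footnote itself applies only to a patient who is otherwise hemodynamically stable, so that condition does not remove the patient from the schedule. The next maneuver is due within an hour, after a disconnection, or before the end of surgery. Nothing in the footnote or the procedure suspends it.

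**Step 6: PEEP changed under the deviation rule.** The triggers are unresponsive hypotension, refractory arrhythmia, vasoactive drugs at the tolerance limit, massive transfusion and a life-threatening surgical complication. In most of these the patient would not meet the stability condition for a maneuver, and the general safety clause allows PEEP to stay where it was set. What is left open is whether maneuvers resume, and at what PEEP, once the patient is stable again.

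**Step 7: how many patients.** The protocol gives no rate for reaching lower-arm step 9, for choosing the optional maneuver, or for footnote reductions. The number affected cannot be derived.

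**The case against.** The best reply is that the procedure was drafted for the higher arm and should be read that way. Step 7 speaks of maintaining PEEP, which presumes a patient already at 12, so it looks like an omission and not an order to raise PEEP. The maneuver is described as part of the protective strategy, and the lower arm is defined without it. The step-9 maneuver is optional, the footnote only asks the clinician to consider a reduction, and the safety clause means that nobody is obliged to restore a PEEP the patient did not tolerate.

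Much of this stands. Omission is the likelier explanation, and the safety clause protects the individual patient. It does not remove the contradiction. The protocol permits a maneuver in the lower arm and offers only this procedure, issued for standardization, for doing it. The safety clause lets a clinician depart from the text but does not say what the text requires.

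Three stronger readings are tempting and should not be adopted:

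- *A reader might infer that the protocol mandates crossover of lower-arm rescue patients.* It does not. Eight of the nine steps carry no maneuver, and the ninth makes it optional. The maneuver at step 9 is itself allowed by design, so only the PEEP difference comes from the conflict.
- *A reader might infer that every permitted PEEP reduction in the higher arm is undone.* Reductions under the deviation rule are largely covered by the stability condition and the safety clause, and a reduction after the last maneuver is not reversed.
- *A reader might infer a loss of power.* That needs a crossover rate and an effect in patients who switch partway through surgery. The documents give neither.

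**Conclusion.** The contradiction is real and confined to two situations: an elected maneuver at lower-arm rescue step 9, and a scheduled maneuver in a higher-arm patient reduced to 10 or 8 under the rescue footnote. Taken literally, the procedure moves PEEP by +5 cmH2O in the first and by +2 or +4 in the second; in the first, the contrast with the assigned higher-arm level disappears.

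This assumes that the procedure applies to every maneuver in the trial, which is how it is introduced, and that no separate instruction exists for patients below 12; the protocol contains none. The number of patients affected is unknown, and variation between sites is a possibility, not something the documents show. The point is a defect in the wording of the intervention, worth correcting because it concerns what was randomized. PEEP changes under the deviation rule need only a cross-reference.

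**What to change.** Reconcile, within section 7.2.2, steps 2 and 7 of the procedure with the lower-arm rescue table and the higher-arm rescue footnote, and add a cross-reference to the deviation rule. The revised text should state:

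1. which PEEP applies during and after a maneuver for a lower-arm patient at rescue step 9;
2. which PEEP applies during and after a maneuver for a higher-arm patient whose PEEP has been reduced;
3. whether scheduled maneuvers continue after such a reduction.

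The clinical investigators must decide the values; this review proposes none.

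No new data collection is needed in principle. Section 7.2.4 already calls for intra-operative variables immediately before and after maneuvers as well as hourly, and PEEP is among them. Because PEEP is listed under a sub-heading that says hourly, confirm that the case report form captures it at the maneuver time points too. Those records, with the rescue and deviation entries already planned, identify patients whose PEEP left the assigned strategy.

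The cost is a few lines of protocol text and a notice to sites, with no extra patients or procedures.

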#### *Protocol deviation*

Anesthesiologists may deviate from the ventilation protocol at any time if concerns about the patient's safety arise, or upon the surgeon's request.

If one of the following complications occurs and is unresponsive to specific conventional therapy, PEEP may be modified according to the anesthesiologist's judgment:

- Systolic arterial pressure lower than 90 mmHg for more than three minutes and unresponsive to fluids and/or vasoactive drugs
- New arrhythmias unresponsive to the treatment suggested by the Advanced Cardiac Life Support Guidelines
- Need for a dosage of vasoactive drugs at the tolerance limit, as judged by the anesthesiologist
- Need of massive transfusion, defined as replacement of >100% blood volume in 24 hours or >50% of blood volume in 4 hours (adult blood volume is approximately 70 mL/kg), to maintain Hct > 21% (Hb > 7 mg/dl)
- Life-threatening surgical complication

#### *Rescue therapy (with the lower PEEP level)*

In case of oxyhemoglobin desaturation ( $SpO_2 \leq 92\%$ ) of a patient in the lower PEEP level group, after exclusion airway problems, auto-PEEP hemodynamic impairment, and ventilator malfunction, a rescue strategy is provided according to the following table:

| Step                                 | FIO 2 | PEEP                       |
|--------------------------------------|------------------|----------------------------|
| 1                                    | 0.5              | 4 cmH 2 O       |
| 2                                    | 0.6              | 4 cmH 2 O       |
| 3                                    | 0.7              | 4 cmH 2 O       |
| 4                                    | 0.8              | 4 cmH 2 O       |
| 5                                    | 0.9              | 4 cmH 2 O       |
| 6                                    | 1.0              | 4 cmH 2 O       |
| 7                                    | 1.0              | 5 cmH 2 O       |
| 8                                    | 1.0              | 6 cmH 2 O       |
| 9                                    | 1.0              | 7 cmH 2 O (+RM) |
| (+RM), recruitment maneuver optional |                  |                            |

### Rescue therapy (with the higher PEEP level)

In case of desaturation ( $SpO_2 \leq 92\%$ ) of a patient in the higher PEEP level group, **it is crucial to exclude hemodynamic impairment as a possible cause**. Also, airway problems, auto-PEEP, and ventilator malfunction must be ruled out as possible causes. Provided those factors are excluded, a rescue strategy is allowed according to the following table:

| Step*                                                                                                                                                                                            | FIO 2 | PEEP                        |
|--------------------------------------------------------------------------------------------------------------------------------------------------------------------------------------------------|------------------|-----------------------------|
| 1                                                                                                                                                                                                | 0.4              | 14 cmH 2 O (+RM) |
| 2                                                                                                                                                                                                | 0.4              | 16 cmH 2 O (+RM) |
| 3                                                                                                                                                                                                | 0.4              | 18 cmH 2 O (+RM) |
| 4                                                                                                                                                                                                | 0.5              | 18 cmH 2 O       |
| 5                                                                                                                                                                                                | 0.6              | 18 cmH 2 O       |
| 6                                                                                                                                                                                                | 0.7              | 18 cmH 2 O       |
| 7                                                                                                                                                                                                | 0.8              | 18 cmH 2 O       |
| 8                                                                                                                                                                                                | 0.9              | 18 cmH 2 O       |
| 9                                                                                                                                                                                                | 1.0              | 18 cmH 2 O       |
| 10                                                                                                                                                                                               | 1.0              | 20 cmH 2 O (+RM) |
| (+RM), recruitment maneuver optional
*At any step: If $SpO_2$ deteriorates further in an otherwise hemodynamic stable patient, consider reducing the PEEP to 10 and then 8 cmH 2 O |                  |                             |

### 7.2.3 Standard procedures

Start of surgery will be defined as the moment of incision for open surgery or insertion of trocars for laparoscopic surgery. End of surgery is the moment of closure of the surgical wound.

Routine general anesthesia, post-operative pain management, physiotherapeutic procedures and fluid management will be performed in the intra-operative and/or post-

operative period according to each center's specific expertise and clinical routine. However, the investigators suggest:

- To use inhalational isoflurane, desflurane or sevoflurane, intravenous propofol, remifentanyl or sufentanyl, and cis-atracurium, atracurium, vecuronium, or rocuronium (as required)
- To use balanced solution of prostigmine, or neostigmine and atropine or glycopyrrolate for reversal of muscle relaxation, guided by neuromuscular function monitoring (for example train-of-four)
- To perform postoperative pain management in order to achieve a VAS pain score below 3. Regional or neuraxial analgesia should be used whenever indicated
- To use physiotherapy by early mobilization, deep breathing exercises with and without incentive spirometry and stimulation of cough in the postoperative period
- To avoid fluid under and overload (according to the discretion of the anesthesiologist)
- To use invasive measurement of arterial blood pressure whenever indicated
- To use appropriate prophylactic antibiotics whenever indicated

Routine intra-operative monitoring should include noninvasive blood pressure measurements, pulse oximetry, end-tidal carbon dioxide fraction and electrocardiography. Every patient should receive at least one peripheral venous line to allow adequate fluid resuscitation during the study period. Nasogastric tubes, urinary bladder catheters and/or other intravenous catheters, as well as other, more invasive monitoring may be used according to local practice and/or guidelines.

Other procedures should follow the Safe Surgery Checklist (see [www.who.int/patientsafety/safesurgery/en/index.html](http://www.who.int/patientsafety/safesurgery/en/index.html)).

#### 7.2.4 Data to be collected

##### *Pre-operative variables*

Pre-operative variables will be collected at the pre-anesthetic visit or before induction of general anesthesia:

- Gender and age; male + years
- Height and weight; kg + cm
- Physical status; according to the American Society of Anesthesiologists (ASA)
- Cardiac status: heart failure, according to the New York Heart Association (NYHA), coronary heart disease, according to Canadian Cardiovascular Society Classification (CCS), atrial flutter/fibrillation
- In patients without known obstructive sleep apnea (OSA), STOP-Bang score

- In patients with known OSA, apnea-hypopnea index (AHI)
- COPD with inhalation therapy and/or steroids; if yes: specify
- Respiratory infection in the last month; if yes: specify upper *or* lower respiratory infection
- Smoking status; never, former (at least three months prior) *or* current
- History of active cancer; if yes, specify type of cancer, classification + therapy
- History of diabetes mellitus; if yes: dietary treatment, oral medication *or* insulin therapy
- History of hypertension
- History of gastroesophageal reflux disease
- Cumulated Ambulation Score  (CAS) to evaluate mobility, see Appendix ii
- Alcohol status in the past 2 weeks; 0–2 drinks/day *or* > 2 drinks/day
- Use of antibiotics in the last 3 months; if yes: specify indication + drug
- Use of statins; if yes: specify type and dose
- Use of aspirin; if yes: specify dose
- Use of oral anti-diabetics; if yes: specify type and dose
- Use of noninvasive respiratory support; if yes: specify if CPAP or NPPV, duration and intensity
- Priority of surgery; elective, urgent, emergency
- Surgical procedure; visceral (biliary, gastric, pancreatic, liver colonic, rectal, other - specify), thoracic (not requiring one lung ventilation - specify), vascular (specify), orthopedic (hip, knee, other - specify), gynecologic (breast, uterus, other - specify), urologic (bladder, kidney, prostate, other – specify), *or* other
- Transfusion, packed red blood cells, fresh frozen plasma, plasma frozen within 24 hours (FP24), fibrinogen, cryoprecipitate, PPSB and platelets in the preceding six hours; if yes: specify type and number of transfused units/amount
- Actual organ function evaluation
  - Respiratory rate
  - SpO2 (10min in room air, beach chair position); %
  - Bedside spirometry (FVC, FEV1) – not mandatory
  - Visual Analogue Scale (10 cm): evaluation for dyspnea, thoracic and abdominal rest and incident pain
  - Airway secretion score: ask patient to cough and subjectively evaluate presence and consistency of sputum; if yes: purulent *or* not
  - Chest X-ray – not mandatory
  - Noninvasive mean arterial pressure; mmHg
  - Heart rate; BPM

- Body temperature; °C
- BUN, Creatinine, AST, ALT, Bilirubin, Hb, Platelets, PT, PTT, WBC count

